The following measures will be used to assess acceptability: the number of participants having completed the program (i.e., ≥ 5/7 sessions) compared to the number of participants connected to the platform (number of drop-outs); the program completion time (from minimum 3 weeks to maximum 8 weeks); the utility of each session, assessed via the VAS after each session; how often the telephone hotline was used; and over the course of the 7 sessions, the relative ratings of perceived stress and self-efficacy and how often subjects practiced the skills associated with each session (Table 1).

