Mid-therapy assessment will take place at 4 weeks after inclusion, i.e., subjects will be asked to fill out depression, PTSD, and COVID-19 infection status questionnaires in order to track potential undesirable outcomes. Eight weeks following their inclusion, participants will receive an e-mail inviting them to fill out all the self-report questionnaires. Then, an e-mail will inform them of the end of the program and of the availability of local mental health services if needed, e.g., psychologists, psychiatrists. Three and 6 months after the end of the program, participants will receive an e-mail inviting them to fill out the follow-up self-report questionnaires. At each step (4-week, 8-week, 3-, and 6-month follow-up), undesirable outcomes will be tracked: i.e., when a participant presents with significant suicidal ideation scores on the 9th item of the PHQ-9 (> 1), the investigator is automatically notified by the website and calls the participant to make the appropriate referrals (e.g., psychiatrist); if a participant is hospitalized in a psychiatric facility during the 8-week treatment phase, he or she will be removed from the study. If a questionnaire is not completed 3 days after it is due, the participant will receive a reminder via an e-mail notification. If questionnaires are not completed a week after they are due, one of the investigators will call the participant and invite him/her to complete it. At any time during the intervention period and after completing the program, subjects are free to withdraw their participation without justifying their motives. No further data will be collected for these participants.

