### CBT intervention: my health too

We developed the CBT program “My Health Too” that consists of 7 video sessions of approximately 20 min, which target the following components identified as key to increasing resilience to stress and preventing mental health problems [27, 28]: (i) psychoeducation [43], (ii) functional behavioral and cognitive coping strategies [43], (iii) mindfulness, (iv) mindfulness/acceptance [44], (v) promoting action toward values [44], (vi) addressing barriers and motivation to use self-compassion as a psychological skill [45], and (vii) self-compassion to soothe difficult emotion [45, 46]. A new session is available every 72 h. Each session is preceded and followed by VAS to aid participants to identify their subjective manifestations of stress and assess the utility of the session. In addition, by the end of each session, participants have the possibility to call a psychologist from the hotline and are invited to practice the strategies learned between sessions through the use of the homework material associated with each video, including mindfulness and relaxation exercises (see Table 2 for the content of the sessions). Whenever a participant does not complete a given session 72 h following the first notification of its availability, he/she will receive an e-mail notification as a reminder. When a participant does not complete a given session 1 week after the first notification of its availability, he/she will be called by an investigator.

**Table 2 Tab2:** Title and content of sessions of the CBT program My Health too

Session number	Session title	Session content
1	The psychological mechanisms of stress	Psychoeducation on Lazarus and Folkman’s [43] transactional stress model; cognitive restructuring
2	Useful behaviors during highly stressful situations	Functional coping strategies (e.g., problem-solving, social support, relaxation, and cognitive restructuring)
3	Mindfulness in everyday life	Mindfulness vs. automatic pilot; mindful observation; 3-min mindfulness practice; letting go of the automatic pilot to improve sleep
4	Dropping the anchor in the present moment to increase resilience	Mindfulness/acceptance skills (i.e., dropping the anchor, cognitive defusion)
5	Engaging in valued actions	Understanding how values are linked to emotions; identification of values, and valued actions

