In order to minimize attrition bias, an intention to treat analysis and specific techniques for handling missing data will be performed. Missing data will be described variable by variable and as a whole in order to search for monotonous patterns. In order to determine the process of generating the missing data (MCAR: missing completely at random, MAR: missing at random or MNAR: missing not at random), dummy variables for whether a variable is missing will be created and cross-tabulated with others observed variables. Multivariate logistic regression can be used to determine a set of variables associated with the probability of observation. In the case of MCAR or MAR processes, multiple imputation methods will be used.

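### The withdrawal rule does not separate stopping the programme from leaving follow-up, so declared withdrawers lose an 8-week PSS-10 score they might have given

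*Protocol article*

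**What the plan says.** The Procedure section of the protocol article says that, during the intervention and after it, "subjects are free to withdraw their participation without justifying their motives". The next sentence is the rule at issue: "No further data will be collected for these participants". Nothing there distinguishes a person who is finished with the programme from a person who is finished with the study.

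People who fall behind without declaring anything are handled differently. An overdue questionnaire leads to an e-mail after 3 days, and after a week "one of the investigators will call the participant and invite him/her to complete it". For the sessions, the section on the CBT intervention says: "When a participant does not complete a given session 1 week after the first notification of its availability, he/she will be called by an investigator". In neither case does missing something remove the person from the study.

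The Statistical analyses section states the aim: "In order to minimize attrition bias, an intention to treat analysis and specific techniques for handling missing data will be performed". On method it adds: "In the case of MCAR or MAR processes, multiple imputation methods will be used".

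**The concern.** An intention-to-treat comparison asks what happened to everyone randomised, including those who gave up the treatment. It therefore needs outcomes from people who stop early. A rule that ends collection for anyone who declares withdrawal turns some obtainable 8-week scores into missing ones. No analysis plan can bring those scores back; it can only make assumptions about them.

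Three features of this trial add to the concern.

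- Participants know their arm, so leaving may reflect how helpful the material seems.
- Only the CBT arm has sessions to fall behind on and investigator calls about missed sessions; none are described for the brochures. Such calls could prompt some people to declare that they are stopping. That is an inference, not something the article reports.
- The primary model uses PSS-10 at baseline and week 8 only. The Procedure text lists depression, PTSD and infection status at 4 weeks. On that text, someone who leaves before week 8 has no post-baseline PSS-10 to inform imputation. Table 1 could show otherwise, but it was not legible in the copy used here.

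If early leavers in the CBT arm do worse than those who stay, and this is not balanced in the control arm, imputing them as if they were stayers makes the programme look better than it is.

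**Working it through.** **Planning figures (Sample size section).** Baseline PSS-10 is 23, with relative falls of 15% and 30%: 23 × 0.85 = 19.55 and 23 × 0.70 = 16.1, given in the article as 19.6 and 16. The falls are 23 − 19.6 = 3.4 (control) and 23 − 16 = 7.0 (CBT), a difference of 3.6. With SD 5, 46 per arm and a two-sided 5% test (sidedness is not stated, so this is assumed), power by the normal approximation is 93.2%. This agrees with the stated power of more than 90%. For a change score, SD 5 corresponds to a baseline-to-week-8 correlation of 0.5, because 5 × √(2 × (1 − 0.5)) = 5. The article does not state the correlation.

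**Who is affected.**

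- Misses sessions, says nothing: reminded and called, and still invited to the 8-week questionnaires, which are timed from inclusion. Not affected.
- Misses questionnaires, says nothing: reminded and called. Not affected.
- Declares full withdrawal from the study: collection stops, which is proper. Not a defect.
- Declares a wish to stop the programme but would still answer questionnaires: no separate route is described, and the rule as written ends collection. **This is the affected group.**

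The wording leaves the last two cases merged. Elsewhere in the Procedure section, participation means active use of the programme over 8 weeks. The withdrawal sentence also covers the period after the programme, where it can only mean leaving the study.

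**Illustration 1: loss in the CBT arm only.** Assume that a share w of the CBT arm withdraws, that these people change like controls (a fall of 3.4), that those who stay fall by 7.0, and that no such loss occurs in the control arm.

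- Difference in all randomised = (1 − w) × 7.0 + w × 3.4 − 3.4 = 3.6 × (1 − w)
- Estimate when the missing are imputed like completers = 7.0 − 3.4 = 3.6
- Overstatement = 3.6 × w

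Results:

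- w = 0.10: difference 3.24, overstatement 0.36
- w = 0.20: difference 2.88, overstatement 0.72

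The range for w is an assumption. Its upper end equals the 20% drop-out allowance in the Sample size section, but that allowance covers all drop-outs and not only declared withdrawals.

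**Illustration 2: withdrawal in both arms.** Let q_E and q_C be the withdrawal shares in the CBT and control arms, and let withdrawers in either arm do k points worse than those who stay.

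- Overstatement = k × (q_E − q_C)

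Results for k from 2 to 7:

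- 20% in each arm: k × 0 = 0
- 25% CBT, 15% control: k × 0.10 = 0.2 to 0.7
- 30% CBT, 10% control: k × 0.20 = 0.4 to 1.4

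In this form the bias exists only if withdrawal differs by arm. It can also arise at equal rates if the loss of benefit differs by arm. If withdrawers in both arms stay at baseline at the same rate w, the overstatement is w × (7.0 − 3.4), again 0.36 to 0.72 for w of 10% to 20%.

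**The case against.** The strongest reply is that the rule concerns withdrawal from the study. It applies after the programme is complete, when there is no programme left to leave, and stopping new data collection is the normal result of withdrawn consent. The reminder and call procedures show that the investigators do pursue people who stop using the material. The acceptability measure counts drop-outs by programme completion without making non-completion an exit from the study. Data collected before withdrawal are not said to be discarded, and a mixed model with multiple imputation can keep all randomised participants under MAR. The missingness will also be examined before imputation, and the 4-week depression and PTSD scores could inform it. The consent form and the full protocol may contain the distinction; neither is shown.

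Most of this stands, and it limits the point to declared withdrawers. A reader might infer that anyone who abandons the sessions is never asked for the 8-week PSS-10. The documents do not support that, because passive non-adherers are still contacted. A reader might also infer that withdrawal has been shown to be related to outcome. It has not: the article gives no withdrawal rates or outcomes by arm.

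What the reply does not remove is that the published rule is categorical and offers no middle route. Examining observed variables cannot show that the unobserved 8-week scores are missing at random. The absence of a stated method for MNAR data is not counted here, since an analysis plan may supply one.

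**Conclusion.** The point holds in a limited form. The withdrawal rule does not separate stopping the programme from leaving follow-up. For participants who declare that they want to stop, the 8-week PSS-10 is lost even if they would have given it. This weakens the intention-to-treat aim. It does not void it, and a reader who concludes that the trial cannot be analysed by intention to treat goes further than the text allows.

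The size is illustrative. With 10% to 20% withdrawal confined to the CBT arm, and withdrawers changing like controls, the overstatement is 0.36 to 0.72 points, that is 10% to 20% of the planned 3.6. Equal rates with equal outcome shifts give zero. A larger figure of 0.7 to 1.4 points (7.0 × 0.10 to 7.0 × 0.20) follows if CBT withdrawers stay at baseline and control withdrawal is ignored. That is a one-sided assumption and should not be read as the expected bias.

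One neighbouring rule bears on the same aim. The Procedure section states that "if a participant is hospitalized in a psychiatric facility during the 8-week treatment phase, he or she will be removed from the study". This exit is plausibly related to outcome, and how these participants' data enter the analysis should be reconciled with the intention-to-treat statement.

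**What to change.** At withdrawal, record which of two decisions the participant makes: (a) stops the programme only, or (b) refuses further questionnaires. For group (a), keep sending the existing 8-week, 3-month and 6-month questionnaires, with the usual reminders, and analyse the answers in the arm to which the person was randomised. For group (b), stop collection as now. Report the numbers in each group by arm.

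The cost is small: one clarified sentence in the protocol and the information sheet, an amendment sent to the ethics committee, and one extra field on the withdrawal form. The questionnaires, e-mails and reminder calls are already in place, and full withdrawal is still respected. The Trial status section says that enrolment had not started at that version of the protocol, so the change could apply from the first participant. If the full protocol or consent form already makes the distinction, aligning the published wording with it is enough.

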### CBT intervention: my health too

We developed the CBT program “My Health Too” that consists of 7 video sessions of approximately 20 min, which target the following components identified as key to increasing resilience to stress and preventing mental health problems [27, 28]: (i) psychoeducation [43], (ii) functional behavioral and cognitive coping strategies [43], (iii) mindfulness, (iv) mindfulness/acceptance [44], (v) promoting action toward values [44], (vi) addressing barriers and motivation to use self-compassion as a psychological skill [45], and (vii) self-compassion to soothe difficult emotion [45, 46]. A new session is available every 72 h. Each session is preceded and followed by VAS to aid participants to identify their subjective manifestations of stress and assess the utility of the session. In addition, by the end of each session, participants have the possibility to call a psychologist from the hotline and are invited to practice the strategies learned between sessions through the use of the homework material associated with each video, including mindfulness and relaxation exercises (see Table 2 for the content of the sessions). Whenever a participant does not complete a given session 72 h following the first notification of its availability, he/she will receive an e-mail notification as a reminder. When a participant does not complete a given session 1 week after the first notification of its availability, he/she will be called by an investigator.

**Table 2 Tab2:** Title and content of sessions of the CBT program My Health too

Session number	Session title	Session content
1	The psychological mechanisms of stress	Psychoeducation on Lazarus and Folkman’s [43] transactional stress model; cognitive restructuring
2	Useful behaviors during highly stressful situations	Functional coping strategies (e.g., problem-solving, social support, relaxation, and cognitive restructuring)
3	Mindfulness in everyday life	Mindfulness vs. automatic pilot; mindful observation; 3-min mindfulness practice; letting go of the automatic pilot to improve sleep
4	Dropping the anchor in the present moment to increase resilience	Mindfulness/acceptance skills (i.e., dropping the anchor, cognitive defusion)
5	Engaging in valued actions	Understanding how values are linked to emotions; identification of values, and valued actions
6	Self-compassion to improve self-care	Psychoeducation on compassion as a psychological skill to soothe difficult emotions and self-criticism [45]; barriers to self-compassion; compassion as a means to self-care
7	Self-compassion to improve emotion regulation	How to use self-compassion to soothe difficult emotions; using self-compassion as a means to self-care; compassion-focused mindfulness [46]

### Active control condition: bibliotherapy

Bibliotherapy consists here of brochures with self-help written relaxation material, which provides low-intensity intervention for stress that should be less efficacious than online CBT [29]. Participants will be able to download these brochures, in a pdf format, via the MaSanteAussi.fr website. The brochures contain psychoeducation as well as written and illustrated instructions to guide relaxation and mindfulness practices. In addition to the written material, people will also have the possibility to call the psychological hotline throughout the 8-week duration of the study.

### Hotline organization

A hotline specifically dedicated to the participants will be set up, run by a team of CBT-trained psychologists. The hotline will be available from Monday to Friday from 9 a.m. to 5 p.m. The psychologists will be trained on the bibliotherapy resources as well as on the CBT “*My Health Too*” online program (a half-day training will be given to them beforehand). They will provide psychological support, advice concerning the skills taught in the program (from either the CBT “My Health too” program or the bibliotherapy brochures), and CBT-based stress management techniques. If the participant presents with more severe psychological symptoms (i.e., severe depression or suicidal ideation), the psychologist will make the appropriate referrals (e.g., psychiatrist). In addition, weekly supervision will be provided by the senior psychologists who created the program. Outside of the hotline’s opening hours, an answering machine will inform participants that they can call the local psychiatric services in case of an emergency.

### Randomization

Randomization will be carried out using the CLEANWEB® software. The randomization will be stratified by the investigation center with a 1:1 ratio for allocation to the 2 groups. Blocks of varying sizes will be randomly selected. The allocation sequence was configured by our data manager who is blinded to the allocation group. Participants will be informed of the group which they are allocated to.

### Statistical analyses

A descriptive analysis will be performed on the entire population and in each group (experimental and control). Categorical variables will be described, giving the numbers and frequency of each modality. Quantitative variables will be described using the usual positional and dispersion parameters. The data analyst will be blinded as he will not participate to data collection.

We will carry out the statistical analysis of the main judgment criterion using a mixed model, including a “group” effect (experimental or control), a time effect (J0 and S8), an interaction between the “group” and the “time,” and a “subjects” effect and a “center” effect. The “subject” and “center” effects will be random effects. The statistical test of interest will focus on the interaction term between group and time, which will assess whether the decrease in the PSS-10 score is greater in the experimental group than in the control group. In a second step, if this test is significant, we will estimate the decrease difference between the groups.

As of the analyses of secondary endpoints, we will assess the efficacy of online CBT on the prevention of PTSD, insomnia, and depression at 3 and 6 months using mixed regression models. In the case of restricted scores with values close to the extremes, we may use beta regression models after transformation of the variable of interest on a scale of ]0;1[. Regarding the predictive factors of the efficacy of online CBT, we will also use the aforementioned models, incorporating an interaction between group, time, and each potential predictive factor to test whether the improvement of scores in the CBT group relies on another factor. Also, we will carry out the identification of potential mediating factors explaining the effect of CBT on professional stress using Bayesian networks that allow learning the structure of a system from the data while integrating hypotheses about the structure. Mediation formulae will be used to assess total, direct and indirect effects. Finally, we will perform a descriptive analysis of the indicators of acceptability and satisfaction.

In order to minimize attrition bias, an intention to treat analysis and specific techniques for handling missing data will be performed. Missing data will be described variable by variable and as a whole in order to search for monotonous patterns. In order to determine the process of generating the missing data (MCAR: missing completely at random, MAR: missing at random or MNAR: missing not at random), dummy variables for whether a variable is missing will be created and cross-tabulated with others observed variables. Multivariate logistic regression can be used to determine a set of variables associated with the probability of observation. In the case of MCAR or MAR processes, multiple imputation methods will be used.

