### Study population

Participants will meet the following inclusion criteria: (1) belong to one of the following professions: medical doctors, nurses, orderlies, physiotherapists, psychologists, hospital porters, ambulance drivers, nursing and medical students working in hospitals; (2) aged 18–70 years old; and (3) fluent in the French language. Exclusion criteria include (1) initial score at the Perceived Stress Scale-10 (PSS-10) [30]< 16 (which means that the participant has a non-significant level of stress), (2) suicidal ideation score assessed by the question 9 of the Patient Health Questionnaire - 9 (PHQ-9) [31] > 2, and (3) be under guardianship. Participants will be recruited by psychiatrists or psychologists in six hospitals of the East region of France, i.e., Hôpitaux Universitaires de Strasbourg, Hôpitaux Civils de Colmar, Groupe Hospitalier Régional de Mulhouse Sud-Alsace, Centre Hospitalier Universitaire de Nancy, Centre Hospitalier Universitaire de Besançon, and Centre Hospitalier Universitaire de Dijon; the East region was the region that was the most affected by the COVID-19 in France. Demographic information (gender, age, family situation), medical history, and occupational exposure (i.e., position, service, seniority on the job, working time, COVID-19 infection status) will be collected.

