### Sample size

The number of subjects required was calculated based on the data from Rose et al. [25] which showed a relative decrease in the PSS-10 score of 15% in the control group and 30% in the experimental group. Mean score values with a standard deviation (< 5) were reported. Given that the healthcare professionals recruited in our study will be under greater stressors than Rose et al.’s [25] study sample, which consisted of college students, the expected values of PSS-10 at baseline are 23 ± 5 with a decrease to 19.6 ± 5 in the control group and 16 ± 5 in the experimental group. Simulations using a mixed linear regression model showed that 46 subjects per group, i.e., 92 in total, would be needed to highlight a difference between groups with a power of more than 90% and an alpha risk set at 5%. Considering an estimation of 10% of exclusions (initial PSS-10 < 16) and 20% of drop-outs, the number of subjects in the study was increased to 120 subjects in total (Fig. 1).

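### The primary test is a valid but unadjusted comparison of mean change in PSS-10: baseline is not a covariate and the center intercept cancels, so precision is lost

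*Protocol article*

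**What the plan says.** All references are to the Protocol article.

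- **Statistical analyses.** The primary model has a group effect, "a time effect (J0 and S8"), the group-by-time interaction, and subject and center effects. "The “subject” and “center” effects will be random effects". On the hypothesis test: "The statistical test of interest will focus on the interaction term between group and time". Baseline PSS-10 therefore enters as an outcome whose mean is free to differ by arm. It is not a covariate, and no center-by-time term is stated.
- **Randomization.** "The randomization will be stratified by the investigation center with a 1:1 ratio for allocation to the 2 groups". Center is the only stratification factor named.
- **Study population.** Eligibility depends on the "initial score at the Perceived Stress Scale-10 (PSS-10"), so a PSS-10 value exists before allocation.
- **Sample size.** "the expected values of PSS-10 at baseline are 23 ± 5 with a decrease to 19.6 ± 5 in the control group", and to 16 with the same SD in the experimental group. Simulations of a mixed linear model are said to give more than 90% power with 46 per group at alpha 5%.

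**The concern.** A pre-randomization PSS-10 has the same expected value in both arms. A model that nevertheless estimates a separate baseline mean for each arm, and then subtracts it in full, spends information on a difference known to be zero in expectation. Unless baseline and week-8 scores are very highly correlated, subtracting the whole baseline adds noise to the week-8 comparison instead of removing it.

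The center term looks like an adjustment for the stratification factor. A random center intercept, however, shifts both of a participant's measurements equally, so it disappears from the within-person change. If centers differ in how fast stress falls, the planned model does not take that up.

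At stake are the precision of the primary estimate and how far the power claim depends on a correlation that the article does not give.

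**Working it through.** **Inputs.** From Sample size: SD 5 at both times, week-8 means 19.6 and 16 (difference 3.6), 46 per arm, alpha 5%. Sidedness is not stated, so two-sided is assumed. The correlation rho is not given, so a range is shown.

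**1. What the interaction test is.** Write each score as fixed part + center intercept + subject intercept + error. In week 8 minus baseline, both intercepts cancel. The interaction is then the difference between arms in mean change.

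This was checked on simulated complete data with 92 subjects, 6 centers, center SD 3 and rho 0.5. In one data set the interaction was -2.706 with SE 0.895 in all three of: the model with center, the model without center, and a plain two-sample comparison of change. Regression of week 8 on arm, baseline and center gave SE 0.789 on the same data. In two further data sets the SEs were 1.077 against 0.983 and 1.066 against 0.830. A simulation with 86 subjects in which centers differed in their change (SD 2) gave SE 1.107 with and without the center intercept, against 0.913 adjusted.

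**2. Variances.**
- Planned: SD of change = 5 × √(2(1 − rho)).
- Adjusted: residual SD = 5 × √(1 − rho²).
- Variance ratio, adjusted to planned = (1 − rho²) / (2(1 − rho)) = (1 + rho)/2.

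**3. The plan's own figure.** With an SD of 5 for the contrast, which is the change SD at rho 0.5, the SE is 5 × √(2/46) = 1.043. Then 3.6/1.043 = 3.45, and power is about 93%. The claim of more than 90% is reproduced at that rho.

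**4. Power at 46 per arm (noncentral t).**

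| rho | SD of change | residual SD | variance ratio | planned | adjusted |
|---|---|---|---|---|---|
| 0 | 7.07 | 5.00 | 0.50 | 68% | 93% |
| 0.3 | 5.92 | 4.77 | 0.65 | 82% | 95% |
| 0.5 | 5.00 | 4.33 | 0.75 | 93% | 98% |
| 0.7 | 3.87 | 3.57 | 0.85 | 99.3% | 99.8% |

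The planned test reaches 90% at rho of about 0.45 (0.43 by a normal approximation). Baseline and center together use about 6 degrees of freedom, which has almost no effect on the adjusted column.

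**5. Sensitivity to the entry cut-off.** If 23 ± 5 describes people before the cut-off at 16, a normal distribution puts about 8% below 16, and truncation lowers the baseline SD to about 4.3 (variance 18.6). Keeping slope rho and residual variance 25(1 − rho²), the variance of change is (1 − rho)² × 18.6 + 25(1 − rho²).
- rho 0.5: 4.66 + 18.75 = 23.41. Ratio 18.75/23.41 = 0.80, a saving of about 20% instead of 25%. Planned power is 94%.
- rho 0.3: 9.13 + 22.75 = 31.88. Ratio 22.75/31.88 = 0.71, a saving of about 29% instead of 35%.

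**The case against.** **The plan is coherent and its test is valid.** The primary outcome is defined as the decrease in PSS-10 at 8 weeks, the test addresses that decrease, and the sample size is said to come from a mixed model. This stands. A reader might infer bias, or an inflated type I error from chance baseline imbalance or from regression to the mean in a sample selected for high stress. The documents do not support that. Selection acts on both arms alike, and chance imbalance is already in the standard error of the change contrast.

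**The stated power may already assume a suitable rho.** A claim of more than 90% from simulation implies a rho of about 0.45 or more, and a condensed article may leave that value to the full protocol. This also stands. The low-rho rows show how sensitive the planned test is; they do not show that the trial is underpowered. At rho 0.7 the gain is negligible.

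**Center is in the model.** A reader might infer that the stratification factor was left out. It was not. It cancels only under an intercept-only reading and with complete or imputed data. When 20% of week-8 values were deleted and not imputed in one simulated data set, the center term moved the estimate slightly (-2.79 with center, -2.91 without). Faster improvement in some centers is a possibility, not something the article reports.

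**Equal baseline means are not assured for every score.** Under Procedure, the depression, PTSD, insomnia, resilience and rumination questionnaires are completed after allocation, and under Randomization participants are told their group. For those scores the objection is right, and it limits the fix. That the baseline PSS-10 in the model is the eligibility value is likely but not stated.

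**Conclusion.** The point holds as one about precision. The planned primary analysis reduces to an unadjusted difference in mean change and makes no use of baseline PSS-10 as a covariate; the center intercept does not contribute to the tested contrast. Adjustment would cut the variance by 35% at rho 0.3, 25% at rho 0.5 and 15% at rho 0.7, or by about 29% and 20% at the first two values if baseline is truncated at 16. The main practical benefit is that power above 90% at 46 per arm would no longer depend on rho.

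This rests on SD 5 at week 8 and, except in the truncated case, at baseline; a difference of 3.6; two-sided 5%; random intercepts only; complete or imputed data; and a PSS-10 measured before allocation. It is a worthwhile improvement to make before enrollment and does not call the validity of the trial into question.

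**What to change.** In Statistical analyses, make the primary analysis a regression of week-8 PSS-10 on arm, with the pre-randomization (eligibility) PSS-10 and center as covariates. The mixed-model equivalent constrains the baseline means to be equal across arms and adds a center-by-time term. State which PSS-10 measurement is the baseline, and report the arm difference at week 8 with its 95% confidence interval.

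Do not carry the equal-baseline constraint over to the secondary scores, because their baseline is recorded after allocation in an open trial.

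The cost is a change of wording and about 6 degrees of freedom (1 for baseline, 5 for six centers). No new data or participants are needed, and Trial status says enrollment had not begun, so the change can still be prespecified.
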